# **Influence of active versus passive parental presence on the behavior of preschoolers with different intelligence and fear levels in the dental operatory: a randomized controlled clinical trial**

## **Abstract**

**Background:** Dental fear and anxiety still pose the most common factors proposed for the child's negative behavior in the dental operatory. Intelligence has an impact on the children's communication, feelings, and responsiveness to dental situations. The benefits of parental presence on reinforcing the child's behavior during dental treatment is still debatable. **Purpose of the Study:** The aim of this study is to assess the effect of parental active versus parental passive presence (PAP/PPP) technique on the overall behavior of preschool children with different intelligence and fear levels. **Methods:** This study will be two-parallel arms randomized controlled clinical trial. One hundred and fifty healthy children, 3-6-year-old, with no history of previous dental pain/treatment, and intelligence quotient (IQ) level of 70 -  $\leq 110$  will be recruited from the outpatient clinic of the Pediatric Dentistry Department, Faculty of Dentistry, Alexandria University, Egypt. In the first visit, the participants will be stratified into 3 equal groups (high, average, low) IQ using the Arabic version of Stanford Binet intelligence scale, fourth edition (SB- IV). In the second visit, dental fear will be assessed using facial image scale (FIS) followed by randomly dividing each IQ group into test and control sub-groups. During intervention, the control sub-groups will be managed using PPP technique, while the test sub-groups will be managed using PAP technique. The dental session will be video recorded and the overall behavior during treatment will be assessed using Frankl behavior rating scale (FBRs) at the end of the second visit.

**Clinical relevance:** This study aims to bridge the gap between the children's social/emotional development and their cognitive development, which has an impact on their behavior in the dental clinic. Moreover, it will also highlight the suitable parental role during treatment whether actively participating or only passively present with his child.

**Keywords:** Behavior modification, Dental fear, Intelligence quotient, Parental active/passive presence, Preschool children, Stanford Binet intelligence scale

## **Introduction & Literature review**

Many practicing dentists have considered the fearful uncooperative child patient as the most troublesome problem in their clinical work.  Fear is a reaction to real or imagined threat and is considered as an integral and adaptive aspect of normal development.  It is a common occurrence characterized by an essential and inevitable emotion that appears as a response to various dental procedures. 

Dental fear has been constantly noticed among children younger than three years, yet it also appears in older children and adolescents.  Various measures have been developed in a bid to develop a uniform method of assessing and grading dental fear in children. Examples of these measures include the Children's Fear Survey Schedule (CFSS) developed by Scherer and Nakamura,  and Dental Subscale of Children's Fear Survey Schedule (CFSS-DS) developed by Cuthbert and Melamed.  These include a questionnaire filled by the child or his parent.  A degree of bias has been reported due to the doubt that the child could not fill out a questionnaire. So various techniques have been developed to circumvent this problem.

Picture scales allow for limited cognitive and linguistic skills. They can be easily administered and scored in a clinical context.  The most developed picture tests are the Facial Image Scale (FIS), and Children's Dental Fear Picture test (CDFP).  The Facial Image Scale uses faces as an indicator of fear. It is also suitable for young preliterate children.  The tool has found to show a high correlation with the Venham Picture Test (VPT) when tested for validity. 

Another worth discussing issue is the child intelligence, which might affect his behavior in the dental clinic. According to Piaget, intelligence is the ability to adapt to the environment. Thought does not develop as do height and weight, which only increase in magnitude with age. Thought assumes qualitatively different patterns at succeeding age levels. 

The term cognition refers to the highest levels of various mental processes such as perception, memory, abstract thinking, reasoning, and problem solving as well as the more integrative and control processes related to executive functions such as planning, choosing strategies, and the enactment of these strategies.  Individuals differ from one another in their ability to understand complex ideas, and to adapt effectively to the

environment. Intelligence was further defined according to two themes: the individual's learning from experience, and the individual's ability to adapt to the environment.

Tests of intelligence come in many forms. Some use only a single type of item or question, such as the Peabody Picture Vocabulary Test (PPVT), and Raven's Progressive Matrices. The more familiar measures of general intelligence-such as the Wechsler Tests and the Stanford - Binet Test include many different types of items, both verbal and nonverbal.

The Stanford – Binet Test (Fourth edition) is based on a hierarchical model of intelligence. The four main areas assessed are Verbal reasoning, Abstract/Visual reasoning, Quantitative reasoning, and Short-term Memory. Fifteen subtests are partitioned in to four main reasoning. The Stanford-Binet IV is a useful test in assessment of a broad range of intellectual abilities. The full battery test is not necessarily used to measure the intelligent Quotient (IQ), an item-reduction short form proved to be a more comparable estimate of the full battery composite.

Simpson and others (2002) evaluated intellectual giftedness in 20 gifted children and 20 non-gifted children. They examined the extent of the difference in IQ scores obtained on the two tests and whether order effects were present using The Wechsler Intelligence Scale for Children–Third Edition (WISC-III) and the Stanford-Binet Intelligence Scale 4th Edition (SB-IV). Results showed that the SB-IV Composite Score was significantly higher than the WISC-III Full Scale IQ for both groups.

A study of children's individual characteristics including age, sex, intelligence quotient and personality variables may help in the understanding of their dental fear. Rud and Kisling (1973) investigated the influence of mental development on children acceptance of dental treatment, by using Banit's, Cattells's, and Leiter's methods on 108 individuals with age of (3-9 years). They reported that children with lower IQs showed more fearful behavior. Savin, and Maxim (2008) carried out a study on 88 subjects (54 girls and 34 boys) aged between 6-8 years old: They divided them into 64 normal subjects from psycho-mental viewpoint and 24 subjects with audio sensory disabilities. They made a complex assortment of investigations: projective draw test (thematic projective test), Raven's progressive matrix test and a questionnaire. The results of all the tests showed that there was a significant correlation between the

IQ level and the behavioral conduct manifested by the child. The subjects with higher IQ level presented a normal conduct. 

Communicative management is an ongoing subjective process that becomes an extension of the personality of the dentist. Associated with this process are the specific techniques of Tell Show-Do technique, Parental presence/absence,  and others.  Parents exert a significant influence on their child's behavior, especially if they have had previous negative dental experiences.  The presence or absence of the parent sometimes can be used to gain cooperation for treatment.  Parents' insistence to be present during their child's treatment does not mean they intellectually distrust the dentist. It might mean they are uncomfortable if they visually cannot verify their child's safety. Therefore, parental presence should not cause any conflict within the dentist. On the other hand, parental presence could be used actively or passively to during dental treatment. 

It is evident that a strong relationship exists between dental fear and children's behavior.  However, limited research has dealt with the effect of children's intelligence on their fear and consequently on their behavior in the dental clinic.  In addition, no research has investigated active versus passive presence of parents in the dental operatory and its effect on the child's behavior. These problems have furnished the stimulus for the present investigation.

### **Hypothesis:**

Null Hypothesis: there is no effect of Parental Active/ Passive Presence Technique and Tell Sow Do (TSD) Technique on the behavior of preschool children with different levels of intelligence and fear.

### **Aim of the study**

This study will be conducted to investigate the effect of parental active/ passive presence technique on the overall behavior of preschool children with different levels of intelligence and fear.

## **Material and Methods**

### **Study Design**

This parallel design randomized controlled clinical trial will be set according to the CONSORT statement.  The PICO question is: In preschool children with different fear and intelligence levels (P) how does parental active presence technique (I) compared to parental passive presence technique (C) affect the children over all behavior during preventive treatment (O)?

### **Study Setting**

The children will be recruited from the Outpatient clinic of Pediatric Dentistry in Faculty of Dentistry at Alexandria University, Egypt

### **Study Sample**

#### ***Sample size estimation***

Sample size was based on assuming 5% alpha error, 20% beta error, allocation ratio between test and control subgroups of 1:1, and probability of positive behavior in the control subgroup of low intelligence quotient (IQ) = 0.25.  An estimation was made of the probability of positive behavior in the test subgroup with low IQ to have positive behavior as healthy children = 0.87.  So, to detect the difference between control and test groups, it was calculated that 9 children per subgroup would be needed.  To ensure adequate power, we estimated a reduction in the difference between test and control groups regarding probabilities of positive behavior of 50% with calculated required number= 24. This was increased to 25 children per subgroup to account for non-completion. Thus, the total required number of children= number of groups X number of subgroups X number per group= 3 X 2 X 25= 150 children.

Visual Screening and parent meeting will be carried out to identify children who will fulfill the inclusion criteria.

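### The 24 children per subgroup do not follow from a 50% smaller difference: the calculation that gives the protocol's own 9 gives 39, and 24 has about 60% power, not 80%

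*Protocol*

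**What the plan says.** All of this is in the Protocol, under Sample size estimation. The error rates are given as "5% alpha error, 20% beta error", with an "allocation ratio between test and control subgroups of 1:1". The control rate is stated as "probability of positive behavior in the control subgroup of low intelligence quotient (IQ) = 0.25", and the test subgroup is expected "to have positive behavior as healthy children = 0.87". From these, "it was calculated that 9 children per subgroup would be needed".

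A margin is then added: "we estimated a reduction in the difference between test and control groups regarding probabilities of positive behavior of 50" per cent, ending in the figure at issue, "probabilities of positive behavior of 50% with calculated required number= 24". The 24 is raised to 25 for non-completion and multiplied by three IQ groups and two subgroups to reach 150.

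The section states neither the sidedness nor the two rates used after the reduction. The Statistical Analysis section plans a chi-squared test of test against control subgroups, plus a logistic regression on IQ group, subgroup and confounders.

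**The concern.** For a comparison of two proportions, the required number grows roughly with the inverse square of the difference. Halving the difference should therefore multiply the number by about four, adjusted for the change in variance. Going from 9 to 24 multiplies it by 2.7, which is too little.

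This number fixes the size of the trial. If it is too small for the effect it is said to cover, the stated 20% beta does not apply to a comparison within an IQ stratum, which is the comparison the section uses for sizing. A non-significant result in the low-IQ group could then be taken as evidence that active parental presence does not help, when the comparison had well under 80% power to show it.

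**Working it through.** **Inputs** (all from Sample size estimation): alpha 0.05, power 0.80, 1:1 allocation, control 0.25, test 0.87, full difference 0.87 − 0.25 = 0.62, halved difference 0.31. Two-sided testing is assumed. The protocol does not state it, but the chi-squared test is non-directional and the two-sided formula is the one that returns 9.

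**Formula** (normal approximation, pooled variance under the null), with p̄ the mean of the two rates and d their difference:

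n = [1.96·√(2p̄(1−p̄)) + 0.8416·√(p1(1−p1) + p2(1−p2))]² / d²

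**Step 1, the protocol's 9.** For 0.25 against 0.87, p̄ = 0.56:

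n = [1.96·√0.4928 + 0.8416·√0.3006]² / 0.62² = (1.376 + 0.461)² / 0.3844 = 8.78, rounded up to 9. This agrees with the protocol. The one-sided version gives 6.79, rounded up to 7.

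**Step 2, the halved difference.** With the control rate held, 0.25 against 0.56, p̄ = 0.405:

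n = [1.96·√0.48195 + 0.8416·√0.4339]² / 0.31² = (1.361 + 0.554)² / 0.0961 = 38.16, rounded up to 39.

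The protocol does not say which rate moves, so the other readings of an exact halving were also run:

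| Rates | n, two-sided pooled | Power at 24 | Power at 25 |
|---|---|---|---|
| 0.25 vs 0.56 (control held) | 38.16 → 39 | 59.5% | 61.3% |
| 0.56 vs 0.87 (test held) | 32.08 → 33 | 67.2% | 69.1% |
| 0.405 vs 0.715 (centred) | 39.05 → 40 | 58.5% | 60.3% |

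Across these three pairs, the unpooled, arcsine and continuity-corrected two-sided versions give 30 to 46.

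**Step 3, power with 24.** For 0.25 against 0.56:

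z = (0.31·√24 − 1.361) / √0.4339 = (1.519 − 1.361) / 0.659 = 0.24, so power is 59.5%.

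Exact enumeration of the Pearson chi-squared test gives 62.3% at 24 and 65.4% at 25. For 0.56 against 0.87 the exact power at 24 is 69.4%. With 39 per subgroup, power for 0.25 against 0.56 is 80.9% by the normal approximation.

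**Step 4, what 24 does support.** From a control rate of 0.25, the formula returns 24 at a test rate of about 0.642. That is a difference of 0.392, and 1 − 0.392/0.62 is a reduction of about 37%, not 50%.

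**Step 5, can any version give 24 for an exact halving?** Among the three pairs above, only a one-sided unpooled calculation at 0.56 against 0.87 does (23.1, rounded up to 24). The same version gives 4.8, rounded up to 5, at step 1, so it cannot be the calculation behind the 9.

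**The case against.** The best defence is that 24 has a source and the sentence is only badly worded. The two-sided pooled formula gives 23.53, rounded up to 24, for 0.50 against 0.87. If the 50% was meant as a control rate of 0.50, then 9 and 24 come from the same formula. This is plausible, but it is inference. The sentence attaches the 50% to the reduction in the difference, and 0.87 − 0.50 = 0.37 is a 40% reduction (1 − 0.37/0.62). It would also double the stated control rate without saying so. The text is wrong as written on this reading too.

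A second objection is that 60% is too exact because the protocol does not fix which rate moves. That is fair. The figure holds with the control rate at 0.25, the only control rate the protocol gives, and the most favourable of the three two-sided readings is 67 to 69% at 24.

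A third is that the practical harm is limited, and this stands in part. For the unreduced 0.25 against 0.87, 24 per subgroup has about 99.9% power. If 0.25 against 0.56 held in every stratum, a comparison pooled over IQ groups, with 75 per arm, would have about 98%. The trial as a whole is therefore not futile. But the protocol justifies its number per subgroup, and the pooled power does not make 24 the right answer to the calculation it states.

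**Conclusion.** The concern holds. The 24 is wrong as written. Under the protocol's own assumptions and the formula that reproduces its 9, a halved difference needs 39 per subgroup (6 × 39 = 234 children before any allowance for non-completion), or 33 to 40 depending on which rate moves.

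With the control rate at 0.25, the real beta at 24 to 25 per subgroup is about 35 to 41%, not 20%. If the control rate is instead raised to 0.56, beta at 24 is about 31 to 33%. These figures assume two-sided testing at 5% and concern the comparison within one IQ stratum. A comparison pooled over strata is not affected in the same way.

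**What to change.** Correct the sample size paragraph as follows:

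- State that the test is two-sided, and give the two rates behind every number quoted.
- State that 24 evaluable children per subgroup give about 60% power for 0.25 against 0.56 (the difference reduced by 50%) and 80% power for 0.25 against about 0.64 (a reduction of about 37%).
- Delete the claim that 24 is the number required for a 50% reduction.
- If 24 was in fact derived from 0.50 against 0.87, say so, describe it as a 40% reduction, and explain why the control rate differs from the stated 0.25.

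The cost is one paragraph and a less favourable power statement. Recruitment, allocation and analysis do not change. The alternative is to keep 80% power for the halved difference, which means 39 per subgroup, or 234 children before non-completion.

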### ***Inclusion Criteria***

1. Age ranging from 3-6 years (the preoperational stage).
2. Patients with at least one sound quadrant.
3. Patients with no history of previous dental treatment and no history of pain
4. Patients with no medical, psychological or mental problems

### ***Exclusion criteria:***

1. Multiple dental problems with pain
2. History of previous dental therapy
3. Medical problem
4. Any degree of mental retardation

### **Ethical Considerations**

Ethical approval will be obtained from the Research Ethics Committee, Faculty of Dentistry, Alexandria University before starting the study. A signed informed consent will be obtained prior to treatment (Appendix I)  after explaining the objectives, risks and benefits of the study to the children's parents/ guardians and after confirming that all provided personal information will be kept strictly confidential.

Parents and children will be provided age-appropriate dental health education and the proper oral hygiene measures including proper brushing twice a day especially before bedtime and proper flossing if indicated will be demonstrated on a model. A fluoridated toothpaste and a brush will be provided to each participant on the day of recruitment.

If the child has any decayed tooth indicated for restoration, it will be restored in visits other than the study visits. All the possible clinical and/ or adverse outcomes will be explained to parents and they will be asked to report immediately if any of them occurs.

### **Randomization and allocation concealment**

Children will be stratified based on their IQ into 3 groups: high, average, and low IQ groups. In each group, children will be randomly and equally allocated according to intervention into test and control sub-groups. The study will thus include

6 subgroups. Randomization will be performed by a trial independent person using computer random number generator. Randomization sequence in blocks of 2 will be created using random allocation software version 1.0.0. The allocated group will be written on piece of paper which will be folded and enclosed in a sealed envelope carrying the child's name on its cover. At the time of intervention, an assistant will open the envelope, identify the sub-group to which the child will be assigned.

### **Calibration and reliability of examiner**

Prior to the study, the researcher will be calibrated by conducting training sessions with the supervisor for the application of the three measurement scales. Intra-examiner reliability will be assessed by the application of Facial Image Scale (FIS) and Frankl's Behavior Rating Scale (FBRS) to 10 children who will not participate in the study then they will be re-evaluated after 5 days. Then the results will be assessed using Kappa statistics.

### **Intervention**

This study will comprise two visits. (Figure 1).

#### **First visit**

Children who will fulfill the inclusion criteria will be evaluated then divided into 3 equal groups according to their level of intelligence IQ by means of Stanford Binet Intelligence Scales, Fourth Edition (SB: IV) - Arabic version (Appendix II) after special training. It is a standardized test that measures intelligence and cognitive abilities in children and adults, from age two through mature adulthood.

The test is grouped into four area scores. The four main areas to be assessed are verbal reasoning, abstract/visual reasoning, quantitative reasoning, and short-term memory. There are 8 subtests selected from the total subtest of Stanford Binet Intelligence Scales according to the age group. The reasoning and the subtests links to.

#### **I- Verbal reasoning (VR):**

##### **1. Vocabulary (V)**

---

 Stanford Binet Intelligence Scales, Fourth Edition - Arabic version: Assessment Course, Steps Training Center, Alexandria. Egypt

2. Comprehension (Com)
3. Absurdities (Ab)

**II- Abstract/visual reasoning (A/VR):**

1. Pattern (P)
2. Copy (Cop)

**III- Quantitative reasoning (QR):**

1. Quantitative (Q)

**IV- Short-term memory (STMR):**

1. Bead memory (BM)
2. Memory for sentence (MS)

**Verbal reasoning (VR):**

The Verbal Reasoning area score measures verbal knowledge and understanding obtained from the school and home learning environment and reflects the ability to apply verbal skills to new situations. Examples of subtests comprising these factor measure skills which include: word knowledge (Vocabulary), social judgment and awareness (Comprehension), and ability to isolate the inappropriate feature in visual material and social intelligence (Absurdities).

**Abstract/visual reasoning (A/VR):**

The Abstract/Visual Reasoning area score examines the ability to interpret and perform mathematic operations, the ability to visualize patterns, visual/motor skills, and problem-solving skills through the use of reasoning. An example of a subtest which determines the Abstract/Visual Reasoning score is a timed test that involves tasks such as completing a basic puzzle and replicating black and white cube designs (Pattern and Copy).

**Quantitative reasoning (QR):**

The Quantitative Reasoning area score measures: numerical reasoning (Quantitative).

### **Short-term memory (STMR):**

The Short-Term Memory score measures concentration skills, short-term memory, and sequencing skills. Subtests comprising this area score measure visual short-term memory and auditory short term memory involving sentences sequences (Memory for sentence). In one subtest that measures visual short-term memory, the participant is presented with pictures of a bead design and asked to replicate it from memory (Bead memory).

### **Test administration**

Administration of the Stanford-Binet Intelligence Scale will take between 45 to 90 minutes (including full battery test). Each selected child will be seated in a private quiet room. The Stanford Binet Intelligence Scale will be applied and explained step by step starting from the first reasoning and its items until the last one.

The first step in this test is to apply the first subtest which is the vocabulary (v) to estimate the *entry level* of the examined child. The child chronological age will be matched with a suitable paragraph (represents a vocabulary photo) according to a placement test's paper in a vocabulary subtest (V). If the child is successful in the paragraph, he will be moved to the next one to finish this level (each level contains 2 paragraphs). This will be considered the *basal level*.

The child will be moved from one level to another until he fails in 5 from 6 paragraphs (fail in 3 consequent levels), which represent the *ceiling level* (cut-off point). The level with right answers in both paragraphs will represent the entry level. It will be considered the starting level in all tests for each subtest.

The test will stop at the ceiling level. Calculation will be counted by subtracting all wrong answers from the number of the last paragraph. A score will be given for each subtest (Raw Scores).

From the standardized tables; after finishing all items, the raw Score (RS) will be changed to Standard Age Score (SAS) by using first type of table. These Scores for each subtest will be collected and change to Reasoning Standardized Score(R-S-S) by using another table. Finally, by using the last type of tables the score will be changed to Compound Score (C-S) which represents the IQ of the examined child.

Children will be divided into 3 groups according to their level of intelligence IQ as follows:

1. High IQ Children (HIQ): with score of (above 110)
2. Average IQ Children (AIQ): with score of (90-110)
3. Low IQ Children (LIQ): with score of (70-89)

Age-appropriate oral hygiene instructions will be given to the children and their parents at the end of the first visit.

